#### Aim 1 (Effectiveness) intervention and control conditions

Schools randomized to the intervention will receive the HSRC initiative immediately, which includes multiple research-based programs shown to improve physical activity, healthy eating, and weight-related outcomes (examples in Table 1). Over the past three years, HSRC has been adopted by more than 50 school campuses across Texas and has reached more than 15,000 students [26]. A detailed description of the HSRC initiative is published elsewhere [24]. Briefly, the HSRC initiative encourages schools to complete a schoolwide walking program, a second program for students, and a program for adults (e.g., teachers or caregivers); however, schools can complete more than three programs. To support the implementation of programs, this study provides each school with a $2,000 stipend, and upon completion, they receive public acknowledgement via a banner and/or proclamations during school board meetings. Schools randomized to the waitlist control condition will maintain their existing practices without adding or removing physical activity or healthy eating programs for students in the 4th through 9th grades. Additionally, they will receive the opportunity to participate in HSRC the following academic year as part of the implementation trial (aim 2).

**Table 1 Tab1:** Examples of Healthy School Recognized Campus’ Evidence-based Programs

Program	Description	Evidence
**Youth**		
Walk Across Texas! (Youth) [28, 29]	An 8-week program designed to help youth across Texas establish the habit of regular physical activity using a fun and motivating team approach	- Doubled the number of steps taken over the course of the program - Increased the amount of time that students were active with their parents - Decreased BMI percentile
Learn Grow Eat & Go [28, 40]	10-week program that teaches students about gardening, healthy eating, and being active	- Increased the number of vegetables tasted, vegetable preferences, and nutrition knowledge - Decreased BMI percentile
Choose Health: Food, Fun & Fitness [41–43]	6-session program that encourages healthy eating and fitness through hands-on activities and experiential education	- Improved overall dietary intake, vegetable intake, fruit intake - Reduced soda/fast food intake - Read nutrition labels and share about healthy eating with families more often - More likely to try new food -Increased frequency of doing physical activities
Color Me Healthy [44, 45]	9-week curriculum extension that focuses on healthy eating and physical activity via coloring, hands-on learning, and music to help children engage with their senses	- Increased fruit and vegetable consumption - Increased students’ knowledge of healthy eating, knowledge about physical activity, and physical activity during the school day
Play Streets [46–48]	Series of 1-day events with various activity stations that promote safe, fun, and active play	- Encouraged physical activity participation - Provided a safe space for outdoor play - Fostered social interaction and community connection
**Adult**		
Walk Across Texas! (Adult) [49]	8-week program designed to help Texans establish the habit of regular physical activity using a fun and motivating team approach	- Increased number of miles walked per week - Decreased leisure time sitting
Cooking Well with Diabetes [50]	3 to 4 lesson workshops that build skills towards planning, preparing, and cooking healthy meals	- Increase fruit and vegetable intake and the use of healthy cooking methods (e.g., baking, broiling, grilling) - Decreased sugar-sweetened beverage intake
Maintain No Gain [51]	6-week holiday challenge to help adults maintain their current weight between Thanksgiving and New Years. Weekly weigh-ins and exercise challenges are provided	- A majority (~ 80%) of participants maintained or improved their weight status during the program

#### Aim 2 (Implementation) implementation strategy and control conditions

Schools randomized to receive the school-to-school mentoring strategy will participate in a series of activities designed to provide a support system, technical assistance, and facilitate connections between schools concurrently implementing HSRC, as a way to improve implementation outcomes (i.e., acceptability, appropriateness, feasibility). Immediately following randomization to the school-to-school mentoring strategy, participating schools will receive an introductory email welcoming them to the school-to-school mentoring program and informing them about its components (e.g., text messages, newsletters). The research team will host virtual meetings with implementers to discuss implementation successes and barriers. Schools will receive quarterly newsletters (up to four times during the year), which will include a previously recognized HSRC school, links to program implementation resources, a spotlighted HSRC program, and local county health-focused events. For agents who report two or more years of experience with HSRC, we will have them co-lead one monthly mentoring meeting and pair them with less-experienced agents to serve as HSRC mentors. Each month, we will send the Extension agent a reminder email and text message of how much of their $2,000 they have spent and how many programs they have completed. By reminding schools of how much money they have left and where they are in the process of getting the HSRC designation, we will continuously engage them with HSRC. Both the intervention and control groups (i.e., standard implementation) will have access to the HSRC website, which includes research evidence and details for each program, alignment of each program with Texas Essential Knowledge and Skills (TEKS) (i.e., curriculum standards for public schools in Texas), step-by-step instructions on how to earn the HSRC distinction, and additional resources.

#### Outcomes

Students will complete data collection two times over the course of the academic year. HSRC implementers will complete data collection three times over the course of the year. For both groups, baseline data collection will occur within the first four months (Aug. 1 – Nov. 30). For implementers, mid-point data collection will occur in the middle two months (January 1 – February 28). For both groups, post-test data collection will occur in the last two months (April 1 – May 31). Student data collection will include a survey, anthropometric assessments, and measures of physical activity and healthy eating at both time points. Students will receive an item worth $20 (e.g., a T-shirt or active toy) for each data collection time point. Data collection for implementers will include a survey at all three points and an in-depth interview post-intervention. Implementers will receive $15 for completing each survey and $40 for completing the interview.

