The Healthy School Recognized Campus (HSRC) initiative directly addresses these implementation challenges by offering a structured framework for schools to adopt and deliver multiple research-based physical activity and nutrition programs [24–27]. Rather than relying on a single curriculum, HSRC bundles complementary programs that collectively support healthier behaviors within the school environment [24–27]. Participating schools commit to implementing at least three research-based physical activity and/or nutrition programs, including: (1) an 8-week walking challenge [28–30], (2) at least one additional program for youth, and (3) at least one program for caregivers, such as parents and/or school staff. A defining strength of HSRC is its multilevel design that aligns with ecological frameworks for health [7, 31, 32]. More specifically, HSRC aims to help health educators who use it engage individuals (i.e., intrapersonal level), social networks (i.e., interpersonal level), and school support (i.e., organizational level) in delivering programs. Schools that complete HSRC also receive public acknowledgement via a banner and/or proclamations during school board meetings, which aligns with prior research showing that such recognition can support improvements in student health outcomes, including body mass index (BMI) [8].

Previous studies have evaluated the effects of the HSRC initiative on student health outcomes and the impact of implementation support strategies on HSRC’s delivery [24–27]. Preliminary data from a single-group pre- to post-test pilot study showed several promising, positive effects of HSRC on the physical activity, nutrition, and BMI z-scores of students [27]. However, a more rigorous study design is needed to better evaluate whether these outcomes are related to HSRC or to other factors occurring during the same period (e.g., the start of the school year) [33]. Similarly, previous work evaluating three different implementation strategies – additional incentives, engaging contests, and school-to-school mentoring – demonstrated that the school-to-school mentoring strategy was a promising approach to improving HSRC’s short-term implementation outcomes (e.g., acceptability, appropriateness, and feasibility) [24]. Nevertheless, it has not been evaluated compared to HSRC’s standard implementation process. As a result, additional rigorous randomized controlled trials are needed.

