### Procedure

#### Randomization

Schools will be randomized to receive one of four conditions: (1) immediate intervention and standard implementation (HSRC + SI), (2) immediate intervention and school-to-school mentoring (HSRC + M), (3) waitlist control and standard implementation one year later (WC + HSRC + SI), or (4) waitlist control and school-to-school mentoring one year later (WC + HSRC + M). To ensure balance across years, schools will be blocked into two cohorts of ten schools, with five receiving immediate intervention and five receiving waitlist control in each of the first two years. Additionally, three schools will receive standard implementation in year one, five in year two, and two in year three, whereas two schools will receive school-to-school mentoring in year one, five in year two, and three in year three (Fig. 1). The order of the ten conditions available each year will be randomized, and schools will receive them based on the order in which they enroll in the study (i.e., signed memorandum of understanding).

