#### Student eligibility and recruitment

Irrespective of the school’s randomized conditions, student recruitment will occur at the beginning of the school's first year of enrollment. Recruitment strategies will include both online (e.g., email) and in-person outreach (e.g., back-to-school events). To be eligible to participate, students must be enrolled in 4th through 9th grade, be between 8 and 16 years of age, and be able to speak, read, and write in English. Students with impairments (e.g., motor, cognitive) or health conditions (e.g., pregnant) that would prevent completion of study assessments will be excluded. Caregivers will complete a consent form and a brief demographic survey at baseline. To consent for the student, caregivers must be at least 18 years old. Students will provide in-person assent before assessments. Students who decline to participate in the study or who are not enrolled by their caregivers will still be encouraged to engage in HSRC programming.

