### Analyses

#### Statistical analysis

For aim 1 (effectiveness), we will use univariate and bivariate statistics to determine the distribution of outcome measures and to identify relevant covariates [61]. To test intervention effects, students randomized to HSRC vs. the waitlist control group (independent variable) will be evaluated using a generalized linear model framework. Baseline scores will be added as a covariate, post-intervention scores as the outcome, and school as a clustering variable [62]. Other covariates (e.g., school size), identified in the preliminary bivariate analyses, will also be included in the model. If missing data occurs, we will mitigate potential biases by analyzing multiple imputed datasets under an intention-to-treat approach [63]. Analyses will be compared to per-protocol analyses [64].

For aim 2 (implementation), we will use a concurrent complementary mixed-methods approach to evaluate the impact of the school-to-school mentoring strategy on each implementation outcome [65]. Quantitatively, we will follow the same analysis approach described for aim 1. However, receiving the school-to-school mentoring strategy (yes vs. no) will be the independent variable, and implementation outcomes (e.g., acceptability, appropriateness, feasibility) will replace student outcomes.

Qualitatively, we will transcribe audio files from the interviews. Applying a directed content analysis and iterative categorization approach [66, 67], we will generate an a priori codebook that is based on our interview guide and the CFIR framework (two coders) [59, 60]. Queries will be performed for quotes assigned to each deductive code, then we will examine the relationship between the implementation strategy, barriers/facilitators, and implementation outcomes. As we are reviewing excerpts from the queries, we will note important findings and key points in ¼ −1-page written summaries. Finalized themes will be produced.

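### The August–November baseline window allows baseline to be measured after HSRC delivery or mentoring contact has begun, and that baseline is then the model covariate

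*Protocol article*

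**What the plan says.** Timing of measurement (Outcomes): "baseline data collection will occur within the first four months (Aug. 1 – Nov. 30", and "post-test data collection will occur in the last two months (April 1 – May 31". Both windows apply to students and to implementers.

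Timing of exposure:
- Randomization: conditions are placed in random order and "schools will receive them based on the order in which they enroll in the study (i.e., signed memorandum of understanding". A school's condition is therefore fixed when it signs.
- Aim 1 conditions: "Schools randomized to the intervention will receive the HSRC initiative immediately". No calendar date is given, and completed baseline is not made a condition of starting.
- Background: the required components include "an 8-week walking challenge".
- Aim 2 conditions: "Immediately following randomization to the school-to-school mentoring strategy, participating schools will receive an introductory email". Monthly reminders to the Extension agent are also part of the strategy.

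Ordering statements:
- Student eligibility and recruitment: "student recruitment will occur at the beginning of" the school's first year, whatever its condition.
- The Abstract places student assessments at the start and end of a school year.
- Implementation outcomes: implementer surveys are to be given ahead of, during and following HSRC. Mentoring is not mentioned in that ordering.

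Analysis (Statistical analysis): "Baseline scores will be added as a covariate, post-intervention scores as the outcome, and school as a clustering variable". Aim 2 follows the same approach with mentoring as the independent variable.

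**The concern.** A baseline covariate is safe in a randomized comparison because treatment cannot have affected it. That protection fails if some baselines are taken after exposure. The adjusted comparison then subtracts part of the treatment effect, which pulls the estimate toward zero and lowers power.

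The window is long enough for this to happen. The walking challenge could begin, and even end, inside it. Table 1 credits the youth walking programme with more steps and a lower BMI percentile, so on the article's own evidence a late baseline could already carry some effect on the primary outcome and on accelerometer activity.

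For aim 2, the first mentoring contact is tied to randomization, while the implementer baseline survey may come at any time up to 30 November.

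A baseline taken after exposure cannot be repaired later, so the order is best fixed before each cohort starts.

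**Working it through.** **1. Dates.**
- The baseline window, 1 August to 30 November, is 122 days, or 17.4 weeks.
- An 8-week programme takes 56 days, so it fits inside the window.
- The interval from baseline to post-test can be as short as 122 days (30 November to 1 April) or as long as 303 days (1 August to 31 May).

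**2. Is an order fixed?**
- Students against the first HSRC session: no sequencing statement. The Abstract and the recruitment section point to the start of the year, but Outcomes defines baseline as the four-month window.
- Implementers against HSRC: yes, the first survey precedes HSRC.
- Implementers against mentoring, which is the aim 2 exposure: no.

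**3. Effect on the adjusted estimate.** Let δ be the final effect, f the average share of δ already present at baseline in the exposed arm, and b the within-arm slope of post-test on baseline. The baseline-adjusted estimate is

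(difference at post-test) − b × (difference at baseline) = δ − b·f·δ = δ(1 − b·f).

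Participants measured before exposure contribute zero to f. For illustration, if half the intervention students are measured after half the effect has accrued and the rest before delivery, f = 0.5 × 0.5 = 0.25. A simulation of 400,000 observations agreed with the formula: at b = 0.9 the retained share was 0.77 for f = 0.25 (formula 0.775) and 0.56 for f = 0.50 (formula 0.55).

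**4. The plan's own figure.** The Power analysis section gives 447 students for power 0.80 on BMI z-score. This cannot be reproduced, because the effect size, variance and cluster effect are not printed. With 25 students per school and two-sided alpha 0.05 (an assumption for aim 1), 447 implies a standardized effect between 0.265 (ICC 0) and 0.393 (ICC 0.05). The next step needs only the stated power, not the effect size.

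**5. Aim 1 power.** With the standard error held fixed,

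power = Φ[(1 − b·f)(1.960 + 0.842) − 1.960].

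Worked case, b = 0.9 and f = 0.25: the retained share is 1 − 0.225 = 0.775. Then 0.775 × 2.802 = 2.171, 2.171 − 1.960 = 0.211, and Φ(0.211) = 0.58.

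| b | f | effect retained | power |
|---|---|---|---|
| any | 0 | 100% | 0.80 |
| 0.5 | 0.10 | 95% | 0.76 |
| 0.5 | 0.25 | 88% | 0.69 |
| 0.5 | 0.50 | 75% | 0.56 |
| 0.9 | 0.10 | 91% | 0.72 |
| 0.9 | 0.25 | 78% | 0.58 |
| 0.9 | 0.50 | 55% | 0.34 |

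Both b and f are assumptions; the article gives neither.

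**6. Aim 2.** The same formula applies, but nothing in the article indicates how much an early mentoring contact moves the acceptability, appropriateness or feasibility scores. No figure can be given.

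**The case against.** The article permits overlap but does not say that it will happen. It gives no start date for HSRC. Its wording on immediate receipt can be read simply as the opposite of waiting a year. A four-month window for a ten-school cohort need not mean a late baseline at any one school, and implementation teams must be formed before delivery can start. Per-school scheduling may also be set out in the full protocol. All of this stands, and it makes the concern conditional. It does not remove it, because the text as written fixes a window that admits baselines after exposure.

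For aim 2, the survey order relative to HSRC is stated. The contact fixed at randomization is a welcome email, the monthly reminders go to the agent rather than the whole team, and the article calls this aim a pilot. These points also stand and suggest that any loss may be small. The stated order still does not cover mentoring.

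A reader might go further and infer that the window does overlap delivery and that power falls to about 65% for a baseline around 1 October, or to 40–45% at 30 November. The arithmetic behind those figures is sound. They require delivery from mid-August, even accrual of the effect over nine months, a slope of 0.90 to 1.00 and every student measured on that late date. The article supports none of these.

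**Conclusion.** The point holds in conditional form. The baseline window allows student baseline after HSRC has begun and implementer baseline after mentoring contact has begun. Because baseline is the covariate in both models, any effect already present would be partly adjusted away.

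The size depends on two unstated quantities. The loss is zero if every baseline precedes exposure. It is modest if a tenth of the effect is present on average, and material from about a quarter upward when the baseline–post slope is high. For aim 2 only the direction can be stated, on the assumption that early contact moves the scores the same way as the final effect. The documents do not support a claim that both treatment effects will be diluted. This is a cheap improvement to the wording and does not show that the trial is compromised.

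**What to change.** Add a sequencing rule to Outcomes:
- At each school, student consent and baseline measures are completed before the first HSRC session and, where feasible, before the school is told its condition.
- The implementer baseline survey in the delivery year is completed before the first mentoring contact, and the welcome email is sent after it.
- Immediate and waitlist schools are measured in the same weeks, so that the interval to post-test does not differ by arm.

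Record the dates of baseline, first session and first mentoring contact. Report by arm how many baselines fell after exposure. Run a sensitivity analysis that does not rely on those baselines, for example a model without the baseline covariate.

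Two alternatives work less well. Withholding allocation until the implementer survey is done does not suit waitlist schools: they must know their status in year one in order to keep their practices unchanged, while their implementer baseline belongs to the following year. Setting late baselines to missing in the primary model would concentrate missing covariate values in the intervention arm.

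Cost: protocol wording and tighter field scheduling. Some schools may begin programming or mentoring contact a few weeks later. No measurements are added.

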##### Effectiveness outcomes

Our primary outcome for evaluating HSRC’s effectiveness (aim 1) is BMI z-score. Secondary outcomes include physical activity and fruit and vegetable intake. Other outcomes that we will measure include waist circumference, blood pressure, and cardiovascular fitness. Students will also complete a survey that includes sociodemographic characteristics (e.g., biological sex, age, grade level, race, and ethnicity).*BMI z-score (Primary)*. Height will be assessed with a portable Seca stadiometer to the nearest 0.5 inch, as the student is standing with feet together, head in the Frankfort plane, and arms hanging naturally at the sides. Weight will be measured using a Tanita body composition analyzer to the nearest 0.1 lb. We will complete measurements up to three times, and the two closest values will be averaged. Measurements will be converted to kilograms (kg) and meters (m), and BMI z-score will be calculated as kg/m2 and compared against normative values from the Centers for Disease Control and Prevention growth charts [52].*Physical Activity (Secondary)*. We will use the ActiGraph GT9X accelerometer (ActiGraph Corporation, Pensacola, Florida, USA) to assess physical activity. Students will be instructed to wear the accelerometer on their non-dominant wrist 24 h a day for seven consecutive days, and to remove the device only for showers or activities in which it could be submerged in water (e.g., swimming, bathing). Raw tri-axial accelerometer data (30 Hz) will be processed into estimates of time spent in light, moderate, or vigorous physical activity [53]. Daily physical activity will be calculated as the sum of all moderate-to-vigorous physical activity and standardized to an 8-h wear period [53]. Student data will be included in analyses if they have ≥ 3 monitoring days in which wear time is > 8 h [53].*Fruit and vegetable intake (Secondary)*. We will assess students’ fruit and vegetable intake using a Veggie Meter, a non-invasive portable device that measures skin carotenoid levels (i.e., a biomarker of fruit and vegetable intake) [54]. We will collect three readings per child, and the average of the three will be used for analysis.*Waist circumference (Other)*. Waist circumference will be measured using a portable measuring tape, containing a Gulick spring attachment, at the midpoint between the floating rib and the iliac crest [55]. Measurements will be conducted three times, and the two closest values will be averaged.*Blood pressure (Other)*. Blood pressure will be measured using an automated Omron sphygmomanometer [56]. Cuff size will be adjusted to match the student's upper right arm. Students will be seated for at least five minutes before the measurement. The measurement will be done up to three times, and the two closest values will be averaged.*Cardiovascular fitness (Other)*. Cardiovascular fitness will be assessed using the FitnessGram PACER (Progressive Aerobic Cardiovascular Endurance Run) test [57]. On this multi-stage shuttle run test, students run twenty meters back and forth to synchronized audio cues. The PACER is sequenced to begin at an initial running speed of 8.5 km/hour and progressively increase by 0.5 km/hour every minute thereafter [57]. A research team member will provide instructions to students in small groups before they complete the test. Cardiovascular fitness is then determined by using laps completed to estimate the maximum volume of oxygen the body can use during intense exercise (i.e., VO₂ max) [57].

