#### Power analysis

For aim 1 (effectiveness), our final sample will include 25 students per school (*n* = 20 schools; 500 students total). With 50% of students in the intervention group and 50% in the control group, using effects sizes, variance, and cluster effects based on prior research [27], calculations indicate 447 students are needed to achieve a power of 0.80 to detect group differences in BMI z-score. We will recruit 500 students to account for a 5% loss to follow up.

Given that we have made additional modifications to the school-to-school mentoring strategy, we consider aim 2 (implementation) to be a pilot cluster randomized controlled trial. Best practices suggest that pilot studies focus on logistics and refinement of implementation protocols, which we will iteratively address through this study [68]. Still, based on our expected recruitment of 20 schools with 8–10-person implementation teams, using a beta of 0.8, a type I error rate of 0.05, and an intraclass correlation coefficient of 0.015–0.030, we are powered to detect a small-to moderate mean difference of 0.25—0.27 points on a 5-point scale (effect size of d = 0.45).

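### Height for the primary BMI z-score is recorded only to the nearest half inch, a small and cheaply avoidable loss of precision that repeat readings do not remove

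*Protocol article*

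**What the plan says.** All of the following is in the protocol article.

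- **Height** (Effectiveness outcomes, BMI z-score): "Height will be assessed with a portable Seca stadiometer to the nearest 0.5 inch".
- **Weight** (same paragraph): "Weight will be measured using a Tanita body composition analyzer to the nearest 0.1 lb".
- **Repeats** (same paragraph): "We will complete measurements up to three times, and the two closest values will be averaged".
- **Derivation** (same paragraph): "BMI z-score will be calculated as kg/m2 and compared against normative values from the Centers for Disease Control and Prevention growth charts". Height therefore enters the primary outcome squared.
- **Analysis** (Statistical analysis): "Baseline scores will be added as a covariate, post-intervention scores as the outcome, and school as a clustering variable".
- **Sample size** (Power analysis): "calculations indicate 447 students are needed to achieve a power of 0.80 to detect group differences in BMI z-score". The plan is to recruit 500 students and allow for 5% loss.

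No finer height resolution is given anywhere else in the article.

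**The concern.** BMI z-score is the only primary outcome of the effectiveness trial, and its two ingredients are recorded with very different care. Weight is read finely, while height, which is squared, is put on a 1.27 cm grid. The repeat-reading rule looks like a safeguard, but repeats on a coarse grid tend to land on the same mark. If three readings split two to one, the two identical values are the closest pair, and the reading that showed the true height to be near a boundary is discarded.

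The rounding enters both visits. It adds noise to the post-test outcome and also to the baseline covariate that is there to gain precision. What is at stake is some power on the primary comparison.

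**Working it through.** **The plan's own figure.** The 447 cannot be reproduced, because the article describes its inputs only as "using effects sizes, variance, and cluster effects based on prior research" and gives no numbers for aim 1. Working backwards with a two-sided alpha of 0.05 (assumed), 447 corresponds to a standardised difference of 0.265 at an ICC of 0 and about 0.38-0.39 at an ICC of 0.05. The dropout allowance is adequate: 447/0.95 = 470.5, so 471 are needed, and 500 × 0.95 = 475 remain. Nothing below depends on how 447 was obtained.

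**Inputs.** From the article: the 0.5 inch and 0.1 lb resolutions, the two-closest rule, the baseline-adjusted model, and the figures 447, 500 and 5%. Students must "be between 8 and 16 years of age". Assumed, because the article gives none of them: heights of 130-170 cm, a weight of 35 kg, LMS reference values S = 0.12-0.16 and L = -2, reader SD of 0.1-0.3 cm, z-score SD of 1, and a baseline-to-post correlation of 0.80-0.97.

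**1. Rounding error in height.** The grid is 0.5 × 2.54 = 1.27 cm. The maximum error is 1.27/2 = 0.635 cm and the SD is 1.27/√12 = 0.367 cm.

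**2. Error in BMI.** Relative error is about 2 × (height error)/height.
- SD: 2 × 0.367/130 = 0.56%, falling to 2 × 0.367/170 = 0.43%.
- Maximum: 0.98% at 130 cm and 0.75% at 170 cm.
- Weight, for comparison: 0.05 lb = 0.023 kg, and 0.023/35 = 0.065% at most. Height rounding is more than ten times larger.

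**3. Error in the z-score.** z error = (BMI/M)^L / S × relative BMI error, at heights of 130-165 cm.
- Near the median: SD 0.03-0.05, maximum about 0.05-0.08, at each visit.
- At BMI 1.3 times the median: SD 0.016-0.028, maximum about 0.03-0.05.

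**4. Do repeats help?** Simulated total error SD in height (cm), taking three readings each time:

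| Reader SD | Half inch, single | Half inch, two closest | 0.1 cm, two closest |
|---|---|---|---|
| 0 | 0.368 | 0.369 | 0.029 |
| 0.1 | 0.382 | 0.375 | 0.083 |
| 0.2 | 0.419 | 0.392 | 0.161 |
| 0.3 | 0.474 | 0.420 | 0.241 |

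The two-closest mean trims some reader noise but never falls below the rounding floor of 0.367 cm.

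**5. Effect on the baseline-adjusted analysis.** With z-score SD 1, correlation ρ and z error SD e at both visits, residual variance without rounding is 1 − ρ². With rounding it is v − ρ²/v, where v = 1 + e². Equivalent N is 447 × the ratio of the two. Power is Φ(2.80/√ratio − 1.96).

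| ρ | e | Variance ratio | Equivalent N | Power |
|---|---|---|---|---|
| 0.80 | 0.020 | 1.002 | 448 | 0.799 |
| 0.90 | 0.035 | 1.012 | 453 | 0.795 |
| 0.95 | 0.035 | 1.024 | 458 | 0.791 |
| 0.95 | 0.045 | 1.040 | 465 | 0.785 |
| 0.97 | 0.045 | 1.066 | 477 | 0.774 |

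Fifteen combinations were run (ρ = 0.80, 0.85, 0.90, 0.95, 0.97; e = 0.020, 0.035, 0.045). Only the last row loses more than 2 power points or needs more than 475 students. The formula treats the rounding errors at the two visits as independent. A student who barely grows between visits carries much the same error twice, which makes the loss smaller.

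**6. Clustering.** Rounding noise adds only to the within-school part of the variance. That part's share of the variance of a school mean is (1 − ICC)/(1 + (m − 1) × ICC), with m = 475/20 = 23.75. As an illustration only, take the ICCs quoted for aim 2: 0.985/1.341 = 73% at 0.015 and 0.970/1.683 = 58% at 0.030. The worst case of 6.6% then becomes about 3.8-4.9%.

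**The case against.** The strongest reply is that the trial still meets its target. Recruitment leaves 475 students against 447 needed, and all but the most extreme assumed combination fits inside that margin. This stands, and it is why the point is minor.

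Three stronger readings are tempting, and the article does not support them.

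- **That the result would be biased.** Height is rounded the same way in both arms and the rounding has no link to allocation. It adds noise and does not shift the group difference.
- **That the loss is reliably around 4-6% of residual variance.** A reader who takes a z error of 0.042 and a residual SD of 0.25-0.30 gets 2 × 0.042²/0.30² = 3.9% to 2 × 0.042²/0.25² = 5.6%. Those residual SDs are not in the article. At 0.40 the same formula gives 2.2%, and at 0.50 it gives 1.4%. The z error is also only about 60% as large at BMI 1.3 times the median (1.3⁻² = 0.59), and the abstract says about a third of U.S. youth are overweight. Even at 3.9-5.6%, the effective number is 475/1.039 = 457 to 475/1.056 = 450, still above 447.
- **That power falls short of the plan.** The variance behind 447 comes from earlier work that is not reproduced in the article. If heights there were recorded in the same way, this noise is already in the 447, and a finer reading would be a gain on the plan. The article does not settle this.

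What survives is narrower. The coarse grid is stated, the repeat rule does not repair it, and the article gives no benefit that would offset the loss.

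**Conclusion.** The point holds as a minor, inexpensive improvement in precision. Half-inch recording is the dominant rounding error in the primary outcome and averaging repeats leaves it in place. It is non-differential and no threat to validity. The cost is about 0.2-6.6% of individual-level residual variance, usually under 2 power points (2.6 in the most extreme assumed case), and less after clustering. The margin of 475 over 447 absorbs nearly all of it.

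The size rests on assumed heights, reference values, reader error, z-score SD and baseline-to-post correlation. The rounding floor of 0.37 cm and the failure of repeats to go below it do not depend on the last two. If half an inch is a misprint for a finer resolution, correcting the text is enough.

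**What to change.** In Effectiveness outcomes, state that height is recorded to the nearest 0.1 cm, or to the finest mark on the stadiometer, at every visit. Keep all individual readings in the dataset, and do the averaging and any unit conversion in software. At 0.1 cm the maximum rounding error in BMI falls from 0.75-0.98% to 0.06-0.08%.

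The cost is a change to the data form, a line of protocol and a short note to assessors. The downside is timing. Registration was in July 2025, publication in February 2026, and baselines run from August to November, so cohort-one baselines may already be in half inches and the lost detail cannot be recovered. In that case change at a point shared by both arms, preferably the start of cohort two, where the Randomization section allocates five schools to each arm. Only later data then gain precision. Report the resolution used in each cohort.
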